### Statistics

Categorical variables will be analyzed using chi-square tests. Ordinal variables will be analyzed using nonparametric tests in addition to using Student’s *t* tests, analysis of variance (ANOVA) and analysis of covariance (ANCOVA) with baseline values as covariates. The time to change in treatment for bipolar disorder will be analyzed using survival analysis. Linear mixed models will be applied in analyses of treatment response. All patients who fulfill baseline registration will be included in the analysis of baseline characteristics. All subjects who receive at least one session of CBT-I and provide post-baseline efficacy measurements will be included in efficacy data analyses. Analyses including only patients fulfilling the treatment will also be conducted.

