[11]. Although evidence of the effectiveness of CBT-I has existed for more than 20 years, it has not been introduced to patients who also suffer from bipolar disorder
[12]. Between-group effect sizes for CBT-I are usually in the range of 1.0 to 1.6, as measured with the Insomnia Severity Index (ISI)
[12,13].

Although it is well documented that sleep is disturbed in bipolar disorder, there is less knowledge about how sleep is disturbed
[3]. There is evidence to suggest that sleep in bipolar disorder is characterized by circadian rhythm disturbance, as in patients with delayed sleep phase syndrome, as well as by maladaptive cognitive and behavioral strategies, as in otherwise healthy individuals with insomnia
[3]. Descriptive studies of frequency and type of sleep disturbance in euthymic patients with bipolar disorder are needed to improve treatment. Data from this trial will be used in a micro- and macroscopic description of the character of sleep disturbance in patients with euthymic bipolar disorder and comorbid sleep disturbance.

Sleep diaries, actigraphy, and, more seldom, polysomnography have traditionally been used to measure the effects of sleep interventions. Polysomnography is considered the best objective monitoring system and the only way to assess the constitution of sleep stages, including changes in slow wave sleep and rapid eye movement sleep, whereas subjective descriptions of sleep quality are better predictors of functional impairment and emotional distress
[11].

The aims of this randomized controlled trial are to compare CBT-I and treatment as usual (TAU) with treatment as usual alone in improving quality of sleep, stabilizing minor mood variations, and preventing new mood episodes in euthymic patients with bipolar disorder and comorbid insomnia. In addition, the study will compare the use of sleep diaries, actigraphy, and polysomnography, in order to possibly simplify registrations of sleep for clinical use.

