1 summarizes the measures to be used in the trial. Patients who have not received psychoeducation for bipolar disorder, either in groups or individually, will be offered such psychoeducation, to ensure that they have received optimal treatment for bipolar disorder. The patients will be rediagnosed for insomnia 6 months after treatment termination. The results of the nights recorded with sleep diaries, actigraphs, and polysomnography will be compared in order to describe the accuracy and clinical utility of sleep diaries and actigraphy compared with polysomnography in bipolar disorder. Participants in the TAU group will be offered standard treatment at the sleep clinic for their sleep disturbances at the end of the six-month follow-up. The included bipolar disorder patients will also be included in a descriptive study of bipolar patients in Norway, the Bipolar Research and Innovation Network- Norway (BRAIN-Norway).

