### Data collection and randomization

Clinical interviews and registrations will be conducted by a psychiatrist, medical doctor, or clinical psychologist at the Bipolar Clinic, Østmarka Department of Psychiatry, St. Olav’s University Hospital, Trondheim, Norway. The insomnia diagnosis will be assessed before randomization, and at a six-month follow-up. The polysomnographs will be administered by the Department of Clinical Neurophysiology at St. Olav’s University Hospital and assessed by a blinded medical doctor. The actigraphy recordings will be administered by the clinician in charge of treatment of each patient. Except for the daily assessments of mood and sleep, the patient-reported measures will be collected using a secure internet-based interface, but patients will be given the option of completing the paper-version of the self-reported measures at the clinic instead.

Patients will be randomized to CBT-I or TAU by a web-based system developed and administered by the Unit of Applied Clinical Research, Norwegian University of Science and Technology (NTNU), Trondheim, Norway. Eligible patients who have signed the consent form and fulfill criteria for participation will be randomized sequentially, in blocks of variable size to ensure an even allocation throughout the study.

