### Treatments

#### *Treatment as usual (TAU)*

This is pharmacological and supportive psychosocial treatment according to the needs and current regime of the patient. The amount of contact with health care professionals outside of our department will be registered. In addition, patients will be offered biweekly consultations with either a psychologist or a medical doctor from our study.

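### The efficacy set requires a CBT-I session, which no TAU patient can meet; on the workable reading it removes non-starters from the CBT-I arm with no matching condition in TAU

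*Protocol article*

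**What the plan says.** The Statistics section names three analysis sets.

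- Baseline: "All patients who fulfill baseline registration will be included in the analysis of baseline characteristics".
- Efficacy: "All subjects who receive at least one session of CBT-I and provide post-baseline efficacy measurements will be included in efficacy data analyses".
- Completers: "Analyses including only patients fulfilling the treatment will also be conducted".

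The rest of the article describes a two-arm randomized comparison. The aim, in Background, is to "compare CBT-I and treatment as usual (TAU) with treatment as usual alone in improving quality of sleep". Under Data collection and randomization, "Patients will be randomized to CBT-I or TAU by a web-based system", and this is done "in blocks of variable size to ensure an even allocation throughout the study". The sample size section compares change in ISI between the groups with an independent-samples t test.

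The TAU arm is described without any CBT-I: "This is pharmacological and supportive psychosocial treatment according to the needs and current regime of the patient". Study design adds: "Participants in the TAU group will be offered standard treatment at the sleep clinic for their sleep disturbances at the end of the six-month follow-up".

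**The concern.** The efficacy rule has two conditions: at least one CBT-I session, and some post-baseline efficacy data.

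By design no TAU patient meets the first condition while outcomes are being collected, so the sentence conflicts with the planned comparison. Someone has to decide what it means before it can be applied.

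The natural repair is to apply the session condition to the CBT-I arm and keep TAU patients who have post-baseline data. That still selects on something that happens after randomization, and in one arm only. A CBT-I patient who never attends is dropped. A TAU patient who would have behaved the same way is kept, because TAU consultations are only offered and no minimum is set. If patients who do not start tend to do worse, the retained CBT-I patients look better than the arm that was randomized. If they tend to do better, the bias runs the other way.

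The condition on post-baseline data is different: it can remove patients from both arms.

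**Working it through.** **Inputs.** From the sample size section: alpha 0.05, 90% power, d = 1.1, ISI 18 versus 14, SD 3.6, total 36. From the randomization section: even allocation, so 18 per arm. Assumed, because the article gives no figures: two-sided testing, the number of non-starters k, and how strongly non-starting relates to outcome.

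**Step 1: the plan's own figure.** n per arm = 2(1.960 + 1.282)² / 1.1² = 2 × 10.51 / 1.21 = 17.4, rounded up to 18, total 36. The stated 36 is reproduced. Exact noncentral-t power at 18 + 18 is 0.894 for d = 1.1 and 0.899 for 4/3.6. The calculation counts both arms in full.

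**Step 2: the sentence as worded.** Of those 36, 18 CBT-I patients could qualify and 0 TAU patients could. No two-group t test can be formed, so the wording and the sample size section cannot both stand.

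**Step 3: power on the workable reading.** With 1, 2, 3 or 4 of 18 CBT-I patients removed and all 18 TAU patients kept, exact power at d = 1.1 goes from 0.894 to 0.884, 0.874, 0.862 or 0.848. The loss is small, so bias is the issue.

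**Step 4: bias on the workable reading.** Take no true effect, 18 per arm, SD 3.6, and remove k CBT-I patients. If the k worst scorers are exactly those removed, the expected shift is

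3.6 × (sum of the k largest expected normal order statistics of 18) / (18 − k).

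- k = 1: 3.6 × 1.82 / 17 = 0.39
- k = 2: 3.6 × 3.17 / 16 = 0.71
- k = 3: 3.6 × 4.24 / 15 = 1.02

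If the tendency not to start correlates r with a poor outcome, the shift is r times that value. For example, 0.3 × 0.39 = 0.12 and 0.5 × 1.02 = 0.51. A simulation of 200,000 trials per cell gives:

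| Correlation of non-starting with poor outcome | False benefit, ISI points (k = 1 / 2 / 3) | Two-sided type I error (k = 1 / 2 / 3) |
|---|---|---|
| 0 | 0 / 0 / 0 | 5.0% / 5.0% / 5.0% |
| 0.3 | 0.11 / 0.21 / 0.31 | 5.1% / 5.5% / 5.7% |
| 0.5 | 0.19 / 0.36 / 0.50 | 5.4% / 6.2% / 7.1% |
| 1 (worst scorers removed) | 0.39 / 0.71 / 1.02 | 6.9% / 10.2% / 15.0% |

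**Step 5: a second parametrization.** If those removed are g SD worse than those retained, the shift is 3.6 × g × k/18. For k = 2, g = 0.5 this is 0.2 points. For k = 4, g = 1.0 it is 0.8 points. Type I error over that range is 5.3% to 9.3%, the same order as the middle rows of the table.

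**The case against.** The strongest reply is that nobody would run the sentence as worded. The aim, the control-group ISI of 18 and the two-group t test all show that TAU patients are meant to be analysed. This stands. A reader might infer that the trial plans an efficacy analysis without controls; the document does not support that.

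The second reply concerns size. The bottom row of the table needs the patients with the worst later outcomes to be exactly those who never attend, yet attendance is settled before outcomes are measured. Many non-starters also seem unlikely, because only patients who complete a three-week run-in of diaries, actigraphy and polysomnography are randomized. This stands too: the bottom row is an upper bound, not an expectation, and even its largest value is well below the planned 4-point difference.

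Third, the rule does not require completion. Withdrawal criteria promises a final evaluation for everyone who discontinues, which may supply post-baseline data for early leavers, although it does not say that the ISI is collected then. So the rule should not be read as dropping everyone who leaves early.

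Fourth, this is a condensed article, and an as-randomized analysis may be described elsewhere. That is why silence on the matter carries no weight here. The point rests on a rule that the article states, and nothing else in it corrects that rule. The planned linear mixed models do not repair it either, because the rule decides who enters them.

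**Conclusion.** The stated rule is wrong and should be corrected, because it fixes who enters the primary comparison. As worded it contradicts the two-arm design, most likely by a slip. On the workable reading it imposes a post-randomization start condition on the CBT-I arm alone. It would be too strong to say that all exclusions fall on one arm, since the data condition can act in both.

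The likely size is modest: about 0.1 to 0.5 ISI points of false benefit and a type I error a little over 5% to about 7%. This rests on 1 to 3 non-starters of 18, SD 3.6, no true effect, and a correlation of 0.3 to 0.5 between non-starting and poor outcome. All of these except the SD and the arm size are assumptions. The upper bound is 0.4 to 1.0 points and about 7% to 15%; with no correlation there is no bias. The sample size figure is not in error.

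**What to change.** Replace the efficacy-set sentence with a definition along these lines: *The primary efficacy set comprises all randomized patients, analysed in the arm to which they were allocated, regardless of the number of sessions attended.* State that all available ISI data are used, including any collected at the final evaluation of patients who discontinue. Keep the at-least-one-session set (with the session condition explicitly limited to the CBT-I arm) and the completer set as supportive analyses.

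The required 36 patients and the primary t test on ISI change need not change. That test still needs an endpoint value, so the already planned linear mixed model can be used to include patients with a missing visit. If the mixed model is to become primary, that is more than a wording change: the plan must say that it replaces the t test and name the primary time point.

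The cost is a rewritten definition and some effort to obtain the ISI from patients who never start. The estimated effect may be slightly smaller because non-starters are included.

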## Ethical approval

The study protocol has been approved by the Regional Committee for Medical Research Ethics in Middle Norway. Written informed consent will be obtained from all included patients.

## Discussion

This study will test whether treatment with CBT-I can provide improvement in sleep quality and will also be one of the first to test the effects of CBT-I on patients with insomnia and bipolar disorder. Insomnia is associated with several negative health outcomes in the general population
[7]. It is likely that patients with bipolar disorder and insomnia, in addition to the same negative consequences, have an increased risk of experiencing new episodes of depression or (hypo) mania.

We are not aware of side effects related to CBT-I, but as it is an untested treatment in bipolar disorder, we do not know if it may trigger new episodes of depression or mania
[35]. The extensive study program may become a potential problem for inclusion of participants and completion of study procedures. Motivational work will be all-important before and during treatment in both groups.

Descriptions of quality of sleep in euthymic periods of bipolar disorder are important for planning interventions and improving monitoring for signs of recurrence of new episodes of depression or (hypo) mania.

It is important to compare the value of diagnostic tools, such as sleep diaries, actigraphs and polysomnography, in order to improve the quality of diagnosis and possibly to simplify the clinical practice of such tools
[36].

### Trial status

Inclusion of patients will start in August 2013 and is expected to continue until January 2015 or until the necessary number of participants has been included.

## Abbreviations

ANCOVA: analysis of covariance; ANOVA: analysis of variance; BAI: Beck Anxiety Inventory; CBT-I: cognitive behavioral therapy for insomnia; BDI: Beck Depression Inventory; DBAS: Dysfunctional Attitudes and Beliefs about Sleep; FFS: Flinders Fatigue Scale; IDWS: Insomnia Daytime Worry Scale; IIS: Insomnia Interview Schedule; ISI: Insomnia Severity Index; MADRS: Montgomery Åsberg Depression Rating Scale; MEQ: Morningness-Eveningness Questionnaire; NEQ: Network Entry Questionnaire for Bipolar Disorder; SCID: Structured Clinical Interview for DSM Disorders; SF-36: Short-Form Health Survey; SHI: Sleep Hygiene Index; SRBQ: Sleep-Related Behaviors Questionnaire; TAU: treatment as usual; YMRS: Young Mania Rating Scale.
